## Abstract

**Background:**

Pakistan has one of the highest maternal mortality ratios worldwide at 276/100,000 live births and only 51% percent of women receive four or more ANC visits. This means that there are missed opportunities for almost half of the women who were not able to seek the recommended antenatal visits. In Thatta district, the maternal mortality ratio is estimated at 313/100,000 live births. Various studies reported that mHealth interventions have proven to be effective to improve antenatal care and postnatal care services. However, the feasibility and effectiveness of mobile health interventions to increase uptake of preventive maternal healthcare services among pregnant women in different settings may be different due to differing patient demographics, cultural diversity, environmental and behavioral factors, availability and accessibility to mobile phones, and budgetary constraints. Prior to implementing a similar intervention in Thatta District, it is crucially important to assess the mobile phone access, usage and willingness among women to receive voice-message based mHealth intervention to improve antenatal care attendance.

**Methods:**

A cross-sectional quantitative study will be used to assess mobile phone access, usage and willingness among women to receive voice-message based mHealth intervention to improve antenatal care attendance in district Thatta. The study will be conducted in Thatta district of Sindh province. Married women of reproductive age (MWRA), who are residing in selected villages of Mirpur Sakro and willing to participate will be included in the study. Multistage sampling technique will be used to recruit the 415 study participants. A structured questionnaire has been designed on Epicollect to collect data from 415 women. Data will be analyzed using IBM SPSS Statistics version 23, with a level of significance as < 0.05.

**Discussion:**

This research project will provide invaluable information on the current access, usage of mobile phones among women of district Thatta and their willingness to receive voice messages to improve the antenatal care services. The study will also highlight demographic, sociocultural and economic factors associated with women willingness and readiness to receive voice messages regarding antenatal care.

## Plain English summary

One out of 140 Pakistani women faces a lifetime risk of maternal death. Most women die because of complications that occur during pregnancy, at delivery, and during the postnatal period. Evidence suggests that antenatal care (ANC) from a skilled provider is important to timely identify and manage preventable maternal morbidities. Several strategies have proven to be effective to improve antenatal care and postnatal care services. However, the effectiveness of these strategies to increase uptake of ANC attendance among pregnant women in different settings may be different due to several factors. Prior to applying a similar intervention in Thatta District, it is crucially important to measure the mobile phone access, usage, and willingness among women to receive voice-message based mHealth intervention to improve antenatal care attendance. A survey will be conducted to assess mobile phone access, usage, and willingness among women to receive voice-message based mHealth intervention to improve antenatal care attendance in district Thatta. This research project will provide invaluable information on the current access, usage of mobile phones among women of district Thatta and their willingness to receive voice messages to improve the antenatal care services.

## Background

In developing countries, women face a lifetime risk of maternal death of one in 160, as compared with 1 in 3700 for women living in developed countries [1]. Pakistan has one of the highest maternal mortality ratios worldwide at 276/100,000 live births [2]. One out of 140 Pakistani women faces a lifetime risk of maternal death [3]. Most women die because of complications that occur during pregnancy, at delivery, and during the postnatal period [4]. Evidence suggests that antenatal care (ANC) from a skilled provider is important to timely identify and manage preventable maternal morbidities such as preeclampsia, eclampsia, antepartum hemorrhage, obstructed labor, postpartum hemorrhage and puerperal sepsis, which are contributing to nearly 70% of all maternal deaths [2]. ANC interventions have proven to be key health interventions to decrease maternal mortality in LMICs, such as Tanzania and Ethiopia [5, 6]. Most importantly, there is need for reinforcement of prevailing evidence-based practices that include World Health Organization (WHO) recommended number of ANC visits (minimum of four ANC visits) to improve maternal health outcomes [7].

The Pakistan Demographic and Health survey (PDHS) 2017–18 shows that only 51% percent of women received four or more ANC visits [8]. This means that there are missed opportunities for almost half of the women who were not able to seek the recommended antenatal visits. In Thatta district, the maternal mortality ratio is estimated at 313/100,000 live births. This estimate is based on a Maternal and Newborn Health Registry (MNHR), which is maintained by Global Network for Women’s and Children’s Health Research Network (GN). A recent trend analysis of ANC showed that the percentages of women receiving at least four ANC visits in Thatta is substantially lower (40%) [9]. To meet the targets of the United Nations’ Sustainable Development Goal 3 by 2030 (maternal mortality ratio < 70/100,000 live births) [10], novel and innovative strategies are required to decrease the rate of maternal mortality by improving the uptake of ANC services. An apparent and accessible strategy to meet this goal is to utilize the potential of simple mobile phones to increase the number of ANC visits (at least 4) among antenatal women.

Various studies reported that mHealth interventions, particularly those delivered through SMS and voice calls, are associated with improved utilization of preventive maternal healthcare services, including uptake of recommended ANC and PNC services. In Njoro Division, a randomized controlled trial evaluated the impact of mobile telephone support on antenatal attendance. A group of 191 pregnant women were regularly given advice and prompts regarding pregnancy care and scheduled antenatal visits through mobile phone; whereas the other groups of 206 pregnant women were provided usual care to continue antenatal visit. Positive association was found among women in intervention group and the number of ANC visits (96.4% in intervention group and 92.3% in the control group, *P* value: 0.002) [11]. A pragmatic cluster randomized controlled trial was conducted in primary healthcare facilities of Zanzibar. The primary outcome measure of the trial was four or more ANC visits. The SMS intervention was related with an improvement in ANC visits in the intervention group. In the intervention group, 44% of women attained four or more ANC visits versus 31% in the comparison group (OR, 2.39; 95% CI 1.03–5.55) [12]. In a rural area of Tamil Nadu, India, a pre-post study was conducted to evaluate whether mobile text messaging service is a feasible mode of raising knowledge level regarding Maternal and Child Health (MCH) services. Data was obtained using a questionnaire in three phases; a) baseline assessment, b) intervention: MCH related messages were sent, c) end line assessment. It was found out that 45 (37.5%) individuals knew about minimum number of antenatal visits during pregnancy after receiving text messages, as compared to 12 (10%) individuals before receiving text messages (*P* value < 0.05, 95% CI: 0.16–0.38) [13]. Three systematic reviews have been conducted on using mHealth applications for improving antenatal and postnatal care in low and middle income countries. All of reviews have reported that mHealth interventions have proven to be effective to improve antenatal care and postnatal care services, especially those that are aimed at changing behavior of pregnant women through SMS and voice messages [14–16].

However, the feasibility and effectiveness of mobile health interventions to increase uptake of preventive maternal healthcare services among pregnant women in different settings may be different due to differing patient demographics, cultural diversity, environmental and behavioral factors, availability and accessibility to mobile phones, and budgetary constraints. Prior to implementing a similar intervention in Thatta District, it is crucially important to assess the mobile phone access, usage and willingness among women to receive voice-message based mHealth intervention to improve antenatal care attendance.

### Scope and objectives

To assess the access and usage of mobile phone among MWRA in district Thatta, KarachiTo determine the willingness of MWRA to receive voice-message based mHealth intervention to improve antenatal care attendance in district Thatta, Karachi

### Operational definitions

Mobile phone access: Access to basic mobile phone or smart phone, mobile phone ownership (self or shared)Mobile phone usage: quantifies the extent to which a person uses a phone, or categorizes the types of uses and situations in which use occursWillingness for mHealth intervention: Women willing to receive voice message to improve ANC attendance. If yes, what are the preferences for language, time to receive voice message etc. If no, what are the barriers or reasons for poor willingness

### Hypothesis

Married women of reproductive age in district thatta, who have access to simple mobile phones, would be willing to receive voice message to improve antenatal care attendance.

## Methodology

### Study design

A cross-sectional quantitative study will be used to assess mobile phone access, usage and willingness among women to receive voice-message based mHealth intervention to improve antenatal care attendance in District Thatta.

### Study setting

Thatta district of Sindh province, lies at the coast of Arabian Sea and is situated about 100 km from the city of Karachi. The total population of district Thatta is about 1 million, which is primarily a rural area (82%). Most people of Thatta speak Sindhi language (87%). About 76% of the population are concentrated in two talukas (sub-districts, Thatta and Mirpur Sakro) of the total of four talukas in the district. The study will be conducted in Mirpur Sakro taluka of district thatta, where Community Health Sciences Department of Aga Khan University has recently established a Rural Health Program (RHP). Mirpur Sakro, is the second biggest taluka of the district in terms of population and has 14 union councils, and 2 town committees. The RHP program is running in 125 villages. The data will be collected from 20 purposively selected villages out of 125 villages. The villages have been divided into three stratas, based on their road distance from health facility (Taulka hospital). The three strata are defined as follows: (i) Villages situated less than 5kms from the health facility (ii) Villages that are 5-10kms away and; (iii) Villages that are more than 10kms away from the health facility.

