### Sample size

Multistage sampling technique will be used to recruit the participants (Fig. 1). According to our best knowledge, we could not find any studies conducted to determine the mobile phone usage and willingness among women to receive SMS text message–based mHealth interventions to improve ANC services in Pakistan, although the mobile phone access in Pakistani women is 39.2%, according to Pakistan demographic and health survey (PDHS) [8]. Therefore, we assumed that 50% of women use mobile phone and are willing to receive voice-message based mHealth intervention for improving ANC services. The maximum sample size is 384, which was calculated using the proportion of women who have mobile phone and are willing to receive voice-message based mHealth intervention for improving ANC services. Considering a 10% nonresponse rate, we calculated the final sample size to be 415. A non-probability purposive sampling will be used to select 415 MWRA, from the households due to lack of availability of household line listing. From each of the 20 villages, households will be selected using proportionate sampling to complete sample size of 415. From beach household, one women will be randomly selected for the purpose of this survey.

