## Discussion

This research project will provide invaluable information on the current access, usage of mobile phones among women of district Thatta and their willingness to receive voice messages to improve the antenatal care services. The study will also highlight demographic, sociocultural and economic factors associated with women willingness and readiness to receive voice messages regarding antenatal care. These insights will guide researchers on how mHealth programs can be tailored to local context, through developing cultural-sensitive messages in local languages, and following societal norms (sending messages on specific time of the day), to ensure successful implementation of such programs. These insights will support decisions on introducing tailored mHealth programs in Thatta and other parts of Pakistan to improve the antenatal care services. While mHealth programs has been proven effective for various chronic diseases and public health issues, it is a novel idea for supporting pregnant individuals for preventative maternal healthcare services, with very few previous studies in area. In this study, if willingness among women is captured towards mHealth intervention, our team will work to implement voice message-based mHealth intervention to improve ANC attendance among women of district.

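### Villages and households are chosen purposively, so the prevalences may be biased by an unknown amount, and conclusions for district Thatta rest on programme villages in one taluka with at most 38% of its population

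*Protocol article*

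**What the plan says.** The protocol article describes the selection in two places.

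- **Villages (Study setting).** "The data will be collected from 20 purposively selected villages out of 125 villages". The 125 are the villages where the Rural Health Program runs, all in Mirpur Sakro, one of the district's four talukas. The section adds: "The villages have been divided into three stratas, based on their road distance from health facility". It states no random draw within these strata.
- **Households and women (Sample size).** The section opens with "Multistage sampling technique will be used to recruit the participants". It then says: "A non-probability purposive sampling will be used to select 415 MWRA, from the households due to lack of availability of household line listing". The next sentence reads "From each of the 20 villages, households will be selected using proportionate sampling to complete sample size of 415", and the last step is that "one women will be randomly selected for the purpose of this survey".

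The target is wider than the frame. Scope and objectives, Hypothesis and Study design all refer to district Thatta. The Discussion promises information on the women of the district and adds: "These insights will support decisions on introducing tailored mHealth programs in Thatta and other parts of Pakistan". It also makes the team's next step, implementing the voice-message intervention, depend on finding willingness in this survey.

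**The concern.** The main results are prevalences: how many women have access to a phone, how they use it, and how many would accept voice messages. A sample prevalence estimates a population prevalence without selection bias only if each woman's chance of inclusion is known and can be allowed for. Here the first two stages are left to judgement. A random choice of one woman inside a household picked by judgement, in a village picked by judgement, does not restore known probabilities. A later analysis plan could not supply design weights either, because there would be nothing to compute them from.

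The justification offered is the missing household listing. That may explain the household stage. It cannot explain the village stage, where the 125 units are already known to the programme.

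The conclusions are also worded for a population most of which lies outside the sampled taluka. If the prevalences are off, the decision on the intervention, and any planning elsewhere in the district, starts from the wrong figure. More interviews would not correct it.

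**Working it through.** **1. The plan's own figure.** Sample size assumes p = 0.50. The article gives neither margin nor confidence level, so I assume d = 0.05 and two-sided 95%:

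n = z² p(1 − p)/d² = 1.96² × 0.25/0.0025 ≈ 384.

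This reproduces the stated 384. The formula is for a simple random sample. (The stated 415 is near, but not equal to, 384/0.9 = 427 or 384 × 1.1 = 423. That does not bear on this point.)

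**2. Which stages are random.**

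| Stage | Rule in the article | Inclusion probability |
|---|---|---|
| Village | purposive, 20 of 125 | unknown |
| Household | purposive, numbers proportionate by village | unknown |
| Woman | random, one per household | known once eligible women are counted |

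The overall probability is the product of the three, so it is unknown.

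**3. Possible bias from the village stage, for the 125-village mean.** Inputs: sampled fraction 20/125 = 0.16 (Study setting); equal village sizes (assumed); gap Δ = mean of chosen villages minus mean of unchosen villages (assumed, as the article gives no figure).

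Bias = mean(chosen) − [0.16 × mean(chosen) + 0.84 × mean(unchosen)] = 0.84 × Δ.

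| Assumed gap Δ | Bias |
|---|---|
| 2 points | 1.7 points |
| 5 points | 4.2 points |
| 10 points | 8.4 points |

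The bias exceeds 5 points, the margin that reproduces 384, only if Δ > 5/0.84 = 5.95 points. Purposive choice of households could add to this or offset it.

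**4. What a bias of that order does.** With n = 415, p = 0.50 and simple-random-sample variance, SE = √(0.25/415) = 0.0245. If a 95% interval were put around the prevalence, its normal-approximation coverage would be about 87% with a bias of 2 points, 47% with 5 and 2% with 10.

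**5. Coverage of the district.** Study setting says that Thatta and Mirpur Sakro talukas together hold about 76% of the population, and that Mirpur Sakro is the second biggest. If Thatta taluka is the biggest, Mirpur Sakro holds at most 76/2 = 38%. If another taluka were bigger, Mirpur Sakro would hold less than the remaining 24%. So at most 38% of the district lives in the sampled taluka and at least 62% outside it. The share living in the 125 villages is not stated and can only be the same or smaller.

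**The case against.** The strongest reply is that the plan is open about this. It calls the household sampling non-probability and gives a reason, it defines the subjects as residents of selected villages of Mirpur Sakro, and it describes a modest feasibility survey. The distance strata reach beyond 10 km, which suggests a deliberate spread of villages. All of that stands. It makes the design understandable, but it does not give the village stage a reason or bring the conclusions down to the frame.

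Several stronger readings are tempting and should not be made:

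- *The plan presents purposive selection as random.* It does not. Random is used only for the woman within the household. Multistage does not imply probability sampling, and a proportionate allocation can be filled purposively as a quota.
- *The Sample size text contradicts itself outright.* It can be read coherently as purposive households followed by a random woman. The sentence that has the women themselves selected purposively is loose and needs rewording.
- *The prevalences will be too high because accessible villages are favoured.* The article describes no convenience mechanism, so no direction can be claimed.
- *Planned confidence intervals for the prevalences are invalid, or a 5-point margin is breached.* The article states neither a prevalence interval nor a margin.
- *The study claims a prevalence for Pakistan.* The Discussion says only that the insights will support decisions elsewhere.

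It is also unclear whether all 125 villages or only the 20 have been sorted by distance. The sampling figure is not shown and might settle that, but it cannot undo the explicit word purposive at both stages.

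**Conclusion.** The point holds. Two of the three selection stages are purposive by the article's own words, so the main prevalences may carry a selection bias whose size and direction cannot be estimated from the data. The stated reason does not reach the village stage. The objectives, hypothesis and discussion name a district of which at least 62% of the population lies outside the sampled taluka.

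The bias figures (1.7, 4.2 and 8.4 points) illustrate assumed gaps with equal village sizes and concern the village stage only. They are not estimates. With a gap below about 6 points the village-stage bias stays under 5 points, so a reader should not infer that the survey is shown to be wrong by more than its margin. What is shown is that the design cannot tell, and that a cheap change would largely remove the problem.

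**What to change.** 1. **Villages.** Draw the 20 at random within the three distance strata from the list of 125, classifying the remaining villages by road distance first if that has not been done. Use one of two matched schemes:
   - equal probability, with the same sampling fraction in each stratum, keeping the proportionate household allocation; or
   - probability proportional to size, with an equal number of households per village.

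   The two should not be mixed. Under probability proportional to size the chance of drawing a village rises with its size, and a proportionate allocation takes the same fraction of households in every drawn village. A household's inclusion probability would then rise with village size, and large villages would be over-represented.
2. **Households.** Use a random start and a fixed interval, which needs no line listing.
3. **Women.** Keep the random choice, record the number of eligible women in each household, and weight by it.
4. **Text.** Reword Sample size so that purposive no longer stands against the random step, and name the rule for each stage.
5. **Conclusions.** Limit objectives, hypothesis and discussion to Rural Health Program villages of Mirpur Sakro. If the 20 villages are already fixed, limit them to those 20.

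No extra interviews are needed. The cost is possibly some travel to less convenient villages, and narrower conclusions. The selection has to be changed before data collection, because it cannot be repaired afterwards. Narrowing the conclusions remains possible at any time.

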### Study subjects

Married women of reproductive age (MWRA), who are residing in selected villages of Mirpur Sakro and willing to participate will be included in the study.

### Sample size

Multistage sampling technique will be used to recruit the participants (Fig. 1). According to our best knowledge, we could not find any studies conducted to determine the mobile phone usage and willingness among women to receive SMS text message–based mHealth interventions to improve ANC services in Pakistan, although the mobile phone access in Pakistani women is 39.2%, according to Pakistan demographic and health survey (PDHS) [8]. Therefore, we assumed that 50% of women use mobile phone and are willing to receive voice-message based mHealth intervention for improving ANC services. The maximum sample size is 384, which was calculated using the proportion of women who have mobile phone and are willing to receive voice-message based mHealth intervention for improving ANC services. Considering a 10% nonresponse rate, we calculated the final sample size to be 415. A non-probability purposive sampling will be used to select 415 MWRA, from the households due to lack of availability of household line listing. From each of the 20 villages, households will be selected using proportionate sampling to complete sample size of 415. From beach household, one women will be randomly selected for the purpose of this survey.

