### Data analysis

Data will be analyzed using IBM SPSS Statistics version 23, with a level of significance as < 0.05
Descriptive: Frequencies, means, and SD will be calculated to describe the variables. Demographic and mobile phone usage data will be compared between respondents belonging to different villages.Inferential: Chi-square and binary logistic regression models will be used to identify factors associated with willingness to use mobile phones for improving antenatal care attendance. Multiple logistic regression will be performed to determine adjusted odds ratio (AOR) for the willingness to use mobile phones for antenatal care attendance; the adjusted variables included residence, ability to read, ownership of mobile phone, routine use of mobile, age group, and duration of mobile phone use.

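### The sample size of 384 assumes simple random sampling, although the survey is a multistage sample over 20 villages, so the precision it implies for the district is not delivered

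*Protocol article*

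**What the plan says.** The relevant text is in three sections of the protocol article.

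- **Sample size, basis.** Finding no earlier study of this question in Pakistan, the authors write that "we assumed that 50% of women use mobile phone and are willing to receive voice-message based mHealth intervention for improving ANC services". The next sentence gives the base figure: "The maximum sample size is 384, which was calculated using the proportion of women who have mobile phone and are willing to receive" the voice messages. Then: "Considering a 10% nonresponse rate, we calculated the final sample size to be 415".
- **Sample size, design.** The section opens with "Multistage sampling technique will be used to recruit the participants". It continues: "A non-probability purposive sampling will be used to select 415 MWRA, from the households due to lack of availability of household line listing", and "From each of the 20 villages, households will be selected using proportionate sampling to complete sample size of 415". One woman is then drawn at random per household.
- **Study setting.** "The data will be collected from 20 purposively selected villages out of 125 villages". Villages are divided into three strata by road distance from the health facility.
- **Data analysis.** The only error level in the document is here: "with a level of significance as < 0.05".

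No margin of error, confidence level, ICC or design effect is given for the sample size.

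**The concern.** The formula that yields 384 treats the women as independent draws from the population. The design takes them in groups from 20 villages. Women in one village share roads, network coverage, household income levels and social norms, so their answers on phone access and willingness are likely to be alike. The protocol itself expects differences between villages: it stratifies them by distance and plans to compare phone use between them. If answers are correlated within villages, 384 women carry less information about the district than 384 independent women.

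At stake is the precision of the proportion willing to receive messages. That proportion is the second objective, and the Discussion makes the decision to implement the intervention depend on it.

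An article may leave many details to a fuller document, but this is not an omitted detail. The printed 384 can be obtained only with a design effect of 1, and the printed design is clustered.

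**Working it through.** **Inputs**

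| Input | Value | Source |
|---|---|---|
| Proportion p | 0.50 | Sample size |
| Base size | 384 | Sample size |
| Final size, non-response | 415, 10% | Sample size |
| Villages k | 20 of 125 | Study setting |
| Confidence | 95% | inferred from the 0.05 level in Data analysis |
| Margin d | 5 points | inferred, see step 1 |
| ICC | 0.01 to 0.10 | assumed; not in the documents |

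**Step 1: reproduce 384.** For one proportion under simple random sampling, n = z² p(1−p)/d².

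- d = 0.05: 1.96² × 0.25 / 0.0025 = 384.15
- d = 0.04: 600
- d = 0.06: 267

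Of these margins only 5 points gives the stated figure, and it does so with a design effect of 1.

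**Step 2: look for an allowance in 415.** A 10% non-response allowance on 384 gives 384/0.9 = 427, or 384 × 1.1 = 423. Both exceed 415, so nothing is left over for clustering.

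**Step 3: allow for clustering.** The average number of women per village is m = 384/20 = 19.2 (415/20 = 20.75 if all respond). These are averages; proportionate allocation makes the actual numbers vary with village size. The design effect is DE = 1 + (m − 1) × ICC = 1 + 18.2 × ICC. The half-width is 1.96 × √(0.25 × DE/384).

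| ICC (assumed) | DE | Effective n (384/DE) | Half-width, points |
|---|---|---|---|
| 0 | 1.00 | 384 | 5.0 |
| 0.01 | 1.18 | 325 | 5.4 |
| 0.02 | 1.36 | 282 | 5.8 |
| 0.05 | 1.91 | 201 | 6.9 |
| 0.10 | 2.82 | 136 | 8.4 |

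For the same four non-zero ICCs, the half-widths are 5.3, 5.7, 6.8 and 8.3 points if all 415 women respond. They are 5.5, 5.9, 7.0 and 8.4 if 10% do not (415 × 0.9 = 373.5).

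**Step 4: what ±5 points would need.** At 19.2 women per village the required number is 384 × DE: 454, 524, 734 and 1,083 women for the four ICCs. With the number of villages held at 20, the effective size cannot exceed 20/ICC. Above an ICC of about 20/384 = 0.052, no number of women per village reaches ±5 points.

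**Step 5: finite-population correction.** If the target is the 125 programme villages, the village sampling fraction is 20/125 = 0.16. Applying it to the between-village part, the variance factor becomes (1 − ICC) + 19.2 × ICC × 0.84. This gives 1.151, 1.303, 1.756 and 2.513, and half-widths of about 5.4, 5.7, 6.6 and 7.9 points. The loss shrinks slightly and does not disappear. The distance strata may also bring a small gain, which cannot be computed from the documents.

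**The case against.** The strongest counter-arguments, and what remains of each:

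- **The protocol never promises ±5 points.** This is true: the margin and the confidence level are both inferred. A reader might infer that a printed precision claim is false, and the documents do not support that. What stands is that 384 has a recognisable basis, and that basis is independent sampling.
- **Any margin is doubtful when selection is purposive.** This also stands. Villages and women are not random draws, so a design effect alone does not yield a valid sampling margin. But the 384 rests on the same random-sampling theory, so the objection weakens the stated basis just as much. It does mean that a restated margin must be called nominal.
- **The target may be only the selected villages.** The Study subjects section defines participants as women living in them. For that population all 20 villages are included, they act as strata, and the between-village term drops out. The objectives, however, name the district, and the point is confined to that wider inference.
- **'Maximum' may simply mean the maximum over p.** That is the natural reading. One might infer that p = 0.5 is no longer the worst case under clustering, but this is wrong: at a fixed ICC and cluster size the variance is p(1−p) × DE/n, which also peaks at 0.5. The word misleads only because a design effect multiplies the size.
- **The effect depends on an unknown ICC, and no decision threshold is stated.** Both are true. At an ICC of 0.01 the loss is under half a point, and no stated rule turns on a margin of 5 rather than 6 or 7 points.

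**Conclusion.** The concern holds in a limited form. The 384 is a simple-random-sample figure with no design effect, and 415 adds non-response only. This conflicts with a multistage sample over 20 villages when the result is read as an estimate for the district.

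With 384 women the nominal half-width is about 5.4 to 8.4 points over assumed ICCs of 0.01 to 0.10, against the 5.0 that the figure implies. It is slightly less with a finite-population correction or a gain from the distance strata. The result rests on inferred 95% confidence and ±5 points, an average of 19.2 women per village, and an ICC range that does not come from the documents.

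A reader might go further and conclude that the survey is too small or must be spread over more villages. The documents do not support that. They set no required margin and no willingness threshold, and say nothing of the field cost of visiting more villages. More villages with fewer women each would improve precision, but that is an optional trade-off.

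**What to change.** Keep the sample. In the Sample size section:

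1. State that 384 assumes simple random sampling, and give the margin and confidence level that were used.
2. Restate the precision as nominal, for example: 'Allowing for clustering in 20 villages with an assumed ICC of 0.01 to 0.10, 384 interviews give a nominal margin of about ±5.4 to ±8.4 points; because villages and households are selected purposively, this does not cover selection bias.'
3. Qualify 'maximum' as the maximum over p under simple random sampling.

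The cost is two or three sentences and no extra interviews. The stated basis becomes less favourable, and the ICC range should be labelled as an assumption.
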